### 3.1.3 Part 3: Registration for a database of bariatric patients for future research

Patients who have agreed to Parts 1 and 2 will be asked if they are willing to be contacted about possibly taking part in other studies. This will not be an obligation to take part, just an expression of interest in being invited to take part. This will create a database of patients who have had bariatric surgery and are willing to consider participation in future research. Ethical opinion will be sought for the development of these study protocols.

## Surgical Obesity Treatment Study

## Glasgow Clinical Trials Unit

### 3.1.4 Service user involvement

SCOTS will uphold the principles embodied by NIHR INVOLVE in relation to user involvement in research, to provide training and support, negotiated roles, time and equitable access for service users involved in this study. SCOTS recruited a patient focus group made of service users who have undergone different procedures both in NHS and private healthcare.

The SCOTS patient focus group have commented on the design of the study, in particular by providing advice on the acceptability of the patient reported outcome questionnaires, the burden to patients and on material and resources that will be given to potential participants. Future sessions are planned to discuss patient recruitment and retention strategies. SCOTS have included a service user on the SCOTS Steering Committee.

## 3.2 Study Population

All patients due to have a bariatric surgical procedure in Scotland will be invited to participate - both NHS and private sector.

A bariatric surgical procedure is defined as a surgical intervention which has the primary purpose of large scale weight loss in a patient who is obese. Currently those procedures include: duodenal switch; gastric banding; gastric bypass and sleeve gastrectomy. The inclusion of emerging techniques in this definition will be decided by the steering committee.

## 3.3 Reference populations

Within this protocol the objectives will be met by comparing before and after surgery outcomes for the SCOTS cohort. Additional funding shall be sought to develop protocols to allow comparisons with the following groups for a final Health Technology Assessment report.

1. SCOTS will compare outcomes with the IT based non-surgical weight management database in Greater Glasgow and Clyde (treatment seeking population with current data on 10,000 patients and 3,000 new referrals per year) which has prospective consent for research allowing data linkage for morbidity and mortality along with adjustment for smoking, deprivation, BMI, age and sex.
2. Standardised mortality ratios are available for a BMI matched cohort from the Scottish Health Survey.

### Surgical Obesity Treatment Study

2017\_11\_22 SCOTS Protocol v1.6

Page 30 of 61

## Glasgow Clinical Trials Unit

3. The Scottish diabetes database allows an anonymous control group matched for key demographics to be created with prospective follow up of diabetes care and complications, compared to those with diabetes who had bariatric surgery.

### 3.4 Inclusion criteria

- Patients aged 16 years or over undergoing their first bariatric surgery in NHS hospitals or private practice in Scotland.
- Capacity to consent
- Resident in Scotland
- Written informed consent

### 3.5 Exclusion criteria

- Does not meet inclusion criteria
- Patients who have had previous weight loss surgery (at time of potential recruitment are undergoing a repeat procedure)
- No written informed consent
- Patients under 16 years
- Patients who do not have capacity to consent for themselves
- Weight loss surgery performed at a site outside Scotland
- Patients who live outside Scotland
- Patients who do not have strong enough English language skills to understand the patient information leaflet without assistance will be excluded from Part 2 of the study, the patient questionnaires. If they require a translator to understand the information they may be able to participate in Part 1 of the study which requires no further interaction from the patient. This decision will be made by the clinical teams caring for patients.

### 3.6 Identification of participants and consent

Patients will be prospectively identified by clinical teams as they are referred for surgery. Patients will be recruited from both NHS and private bariatric surgical practice in Scotland. They will either be recruited by a member of the surgical team prior to undergoing a bariatric surgical procedure, including any significant pre-operative weight loss (such as a very low energy diet for liver shrinkage or use of an intra-gastric balloon) which is considered part of the surgical pathway, or the surgical team will ask the patient's permission to pass over their name and contact details to the SCOTS research team who will then contact the patient directly to give further information and obtain fully informed consent.

#### Surgical Obesity Treatment Study

2017\_11\_22 SCOTS Protocol v1.6

Page 31 of 61

## Glasgow Clinical Trials Unit

Depending on local patient pathways patient information sheets will be provided to patients at a clinic visits or group session. This will be provided at least 24 hours before the patient will be asked to consent. In the case of those patients who are to be recruited by the research team (identified by surgical team), a patient information sheet will be provided when the permission is sought to hand over contact details to the research team. Patients who meet the eligibility criteria will be identified by their local clinical care teams. All patients undergoing bariatric surgery will be recorded on the screening log at their next appointment. This will allow patients to consider their participation and ask any additional questions they may have about the study face to face. An independent contact is provided on the patient information leaflet who patients can contact to discuss participation in research studies.

They will be asked to give fully informed consent for clinical data linkage (Part 1) and to be contacted by Glasgow University by post, email or phone about to completing the Patient questionnaires (Part 2) and for permission to contact them about future studies (Part 3). Patients who require a translator will only be asked to participate in Part 1. Only patients who agree to Part 1 will be eligible for Part 2 or Part 3.

## 3.7 Withdrawal of subjects

Participants have the right to withdraw from the study at any point for any reason. The SCOTS web site and patient information sheets will provide contact details for patients if they wish to withdraw from the study. If patients have asked to complete the forms by paper, contact details will be included within each paper questionnaire. The SCOTS team will provide patients with a form to complete, if they are contacted with a request to withdraw from the study.

If the SCOTS team are contacted by a patient who no longer wishes to participate in the study, they will be contact by the SCOTS team at University of Glasgow and asked to specify which following options they would like to apply to their data:

- A. (For those within Part 1) I no longer wish to continue the study but I am content to allow my existing data to remain within the study for analysis.
- B. (For those consented to Part 1 and 2). I am content for my records to be linked but I no longer wish to complete the patient questionnaires.
- C. (For those consented to Part 1, 2 and 3). I am content for my records to be linked but I no longer wish to complete the patient questionnaires or be contacted regarding future studies.
- D. For any patient I would like to completely remove my all data from the study and wish not to be contacted again by the study.

## Surgical Obesity Treatment Study

## Glasgow Clinical Trials Unit

When a request is received from a patient to withdraw from the SCOTS study, a standardised form will be sent to the patient by their preferred communication route. The form will be completed by the patient including the patients name date of birth and address, and the on receipt data manager will flag the patient as having withdrawn from the study. The patient will be asked if they would like to be informed of the findings of the study even though they will no longer be participating in the study.

## 4 STUDY PROCEDURES

The study design involves local clinical teams identifying and potentially recruiting participants (some participants will be recruited by the SCOTS research team after identification by the local clinical team). Patients who consent to participate will have recruitment data collected by their clinical care teams or the SCOTS research team. Following their operation patients will have their weight loss surgery details entered into the database. The clinical teams then use the system to include follow up weights and re-operations. For the remainder of the study, patients who have consented to part 2 of the study will be asked to complete questionnaires and their health outcomes will be recorded by record linkage to routine data sets. A detailed breakdown of patient contacts with the study is described in Table 4-1 below.

**TABLE 4-1: SCOTS PATIENT VISIT SCHEDULE: DESCRIBES EACH INTERACTION WITH PATIENTS IF THEY CONSENT TO PART 1 AND 2 OF THE STUDY.**

| Patient contact | Time                              | Routine care                                                                                                                                             | SCOTS                                                                                                                                                                                                                  | Part 1 | Part 2 | Part 3 |
|-----------------|-----------------------------------|----------------------------------------------------------------------------------------------------------------------------------------------------------|------------------------------------------------------------------------------------------------------------------------------------------------------------------------------------------------------------------------|--------|--------|--------|
| 1               | 1 year to 6 weeks before surgery  | Agree bariatric surgery                                                                                                                                  | Patients given/sent Invitation to participate letter and patient information sheet (and asked if they are to be contacted by SCOTS research team for further information and informed consent if no local recruitment) | 1      | 1      |        |
| 2               | 1 year to 6 weeks before surgery  | Patient pre-surgical clinic visit, dietician, psychologist if local recruitment; phone call from SCOTS research team member if research team recruitment | Patients asked if they are willing to consent to participate in SCOTS, Patient signs consent forms, clinical team and patient complete contact details and baseline height and weight.                                 | 1      | 1      |        |
| 3               | At least one month before surgery |                                                                                                                                                          | Patient contacted by SCOTS team to complete pre-operative questionnaire                                                                                                                                                | 1      | 1      |        |
| 4               | Date of surgery                   | Patient has weight loss operation                                                                                                                        | Clinical team enters details of weight loss operation to SCOTS portal                                                                                                                                                  | 1      | 1      |        |

### Surgical Obesity Treatment Study

## Glasgow Clinical Trials Unit

|       |                              |                                                                                       |                                                                                                                                                |   |   |   |
|-------|------------------------------|---------------------------------------------------------------------------------------|------------------------------------------------------------------------------------------------------------------------------------------------|---|---|---|
| 5     | Patient admitted to hospital | Identified by record linkage                                                          | If patient hospital admission is possibly related to bariatric surgery, patient will be contacted by SCOTS Team.                               | 1 | 1 |   |
| 7     | At routine follow up visits  | Patients attend routine clinical visits                                               | Clinical teams enter weight and re-operation details                                                                                           |   | 1 |   |
| 8     | Two year post surgery        | Patients have routine annual blood test and results are made available via SCI-store. | Patients complete two year post surgical questionnaire                                                                                         |   | 1 |   |
| 9     | Three years post surgery     | Patients have routine annual blood test and results are made available via SCI-store. | Patients complete three year post surgical questionnaire                                                                                       |   | 1 |   |
| 10    | Any point after recruitment  |                                                                                       | Possibly contacted to participate in future studies                                                                                            |   |   | 1 |
| 11    | Three years onward           | Patient continues to have routine annual blood test every year                        | Patient contacted to thank them for completing the PROMS. Record linkage continues. Patients will be informed about future SCOTS publications. |   | 1 |   |
| Total |                              |                                                                                       |                                                                                                                                                | 5 | 9 | 1 |

Figure 4-1 shows what happens at each point within the study. This includes background record linkage and patient contacts.

FIGURE 4-1: BASELINE – PRIOR TO OPERATIVE WEIGHT LOSS (INCLUDING PRE LIVER-PREP DIET OR BALLOON PHASE)

[figure not shown]

## Surgical Obesity Treatment Study

2017\_11\_22 SCOTS Protocol v1.6

Page 34 of 61

Glasgow Clinical Trials Unit

FIGURE 4-2: 2 AND 3 YEARS POST DEFINITIVE SURGERY

[figure not shown]

## Glasgow Clinical Trials Unit

FIGURE 4-3: PART 3 IF NEW BARIATRIC SURGERY STUDY BEGINS

[figure not shown]

## 4.1 Duration of participation

Part 1: if funding is available, record linkage, follow up of patients will continue throughout their life. The end of a patient's life will be shown by linkage to the GRO data set. This will be used to flag deceased patients.

Part 2: patient reported outcome measures (PROMS) questionnaires will be collected for a maximum of 3 years. Collection of PROMS will stop after December 2020.

Part 3: Patient contact details will be kept by the study team until the end of the patient's life. The end of a patient's life will be shown by linkage to the GRO data set. This will be used to flag deceased patients and they will be removed from the database in Part 3 to ensure patients families are not contacted after their death. Patient will only be contacted for future studies if record linkage is available to show that they are still living.

Patients will be able to withdraw from the study at any point. Data collected will be retained unless explicitly requested to be removed from the study by the patient.

## Surgical Obesity Treatment Study

Glasgow Clinical Trials Unit

4.2 Study schedule

This section provides a brief overview of the procedures for investigators at each point within the study. SCOTS will integrate into routine care pathways for bariatric surgery as much as possible. No additional clinic visits will be required. There are five points within the patient journey that the clinical/research team are required to undertake any tasks. These points are described in detail in the following sections.

4.2.1 Start of Study - Surgical team registration

Each site will be defined before the start of the study and login and passwords will be created for each principal investigator and their clinical teams.

A training plan will be developed for clinical teams. Clinical teams will be provided with an overview of the study provided with a training package which will be developed electronically, to be completed at their convenience, electronic guidance will be integrated into the data collection tool to assist them. A user manual will be created which will explain the data which is required for each field and define each data field.

An electronic form will be used to collect surgeon specific data the first time they log onto the bariatric data collections system. This form will be developed by the study Data Centre at the Robertson Centre for Biostatistics, University of Glasgow and access to the form will be restricted, with only authorised site-specific personnel able to make entries or amendments to their data. A manual will be developed to assist investigators with use of the electronic data collection system. It is the investigator's responsibility to ensure completion and to review and approve all data captured. Surgeons will be asked to outline which locations they work in, which procedures they use, and the details of these procedures. They will also be asked information on their surgical experience including date when they qualified, number of procedures the previously year, total number of procedures undertaken in the last five years.

The aim of this task is to ensure that surgeons' data is entered at the start of the study and patient records can be pre-populated to ensure that data can be collected as efficiently as possible.

|                                                                                                        |  |
|--------------------------------------------------------------------------------------------------------|--|
| Checklist:                                                                                             |  |
| Surgeon registers on SCOTS system                                                                      |  |
| Surgeon enters names and email addresses of clinical team who will be part of SCOTS investigators team |  |
| Investigators have the opportunity to view SCOTS training materials                                    |  |
| SCOTS resource pack is available at the site                                                           |  |

Surgical Obesity Treatment Study

## Glasgow Clinical Trials Unit

**4.2.2 Visit 1 Routine care invitation visit**

Patient pathways vary throughout Scotland, invitation and introduction should take place at either an individual's clinic visit or at a group session discussing weight loss surgery. The aim of this visit is to ensure that patients who are planning weight loss surgery are aware of the SCOTS study, why it is being undertaken and what would be required from them.

**4.2.2.1 Invitation visit protocol (in sites with local team recruitment)**

1. Patient attends routine clinic to discuss bariatric surgery with clinical team.
2. Patient provided with an overview of SCOTS
3. Patient provided with opportunity to ask initial questions
4. Patient provided with invitation to participate in SCOTS and patient information leaflet (pre-prepared pack).

|                                              |  |
|----------------------------------------------|--|
| Checklist:                                   |  |
| Patients provided with overview of SCOTS     |  |
| Patient provided with SCOTS information pack |  |

**4.2.2.2 Invitation visit protocol (in sites with SCOTS research team recruitment)**

5. Patient attends routine clinic to discuss bariatric surgery with clinical team.
6. Patient provided with a summary overview of SCOTS
7. Patient provided with invitation to participate in SCOTS and patient information leaflet (pre-prepared pack).
8. Patient asked permission for surgical team to pass on contact details to SCOTS research team
9. Participant Identification form completed and returned to research team

|                                                                              |  |
|------------------------------------------------------------------------------|--|
| Checklist:                                                                   |  |
| Patients provided with a summary overview of SCOTS                           |  |
| Patient provided with SCOTS information pack                                 |  |
| Permission sought and Participant Identification Form completed and returned |  |

**4.2.3 Visit 2 Recruitment visit**

At the next follow up clinic appointment patients will be asked if they wish to take part in SCOTS. Patients must have been given more than 24 hours to consider their participation.

**Surgical Obesity Treatment Study**

## Glasgow Clinical Trials Unit

For patient's in sites where recruitment is carried out by the SCOTS research team the following will occur after the research team receive the participant information form from the local site:

1. SCOTS research team contact patient via telephone
2. Patient provided with an overview of SCOTS
3. Patient provided with opportunity to ask initial questions

Details of all patients who plan to have bariatric surgery will be recorded on a screening log. These logs will be recorded on paper. Every patient who plans bariatric surgery will be logged anonymously with details of the individual's age category on date of invitation, gender, calendar quarter surgery planned, if they meet the SCOTS eligibility criteria, if they consent and type of surgery planned (for participants identified via local sites but recruited by the SCOTS team only those giving permission for their details to be forwarded to local teams will have a screening log completed as the research team shall do this). The purpose of this log is to demonstrate if the SCOTS data set is representative of all patients who are having bariatric surgery in Scotland. It will also provide a record of number of patients who consent. A copy of the screening logs will be sent to the Robertson Centre on an annual basis.

This is an anonymised screening record and patients who do not wish to participate will have no further information collected.

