### 4.2.3.2 *Informed consent protocol (in sites with SCOTs research team recruitment)*

1. When the Participant Identification Form is received from the surgical team start to complete the SCOTs Recruitment Log and contact the patient via telephone.
2. Ask the patient if they have any questions relating to the study documentation. Ensure that the patient fully comprehends the information given.
3. Explain that participation is voluntary and should they decide to proceed with participation in the study, they are free to withdraw at any time without giving an explanation.
4. Complete the screening log (do not add participant ID as form is to be anonymous)
5. If a patient chooses to decline, thank them for their time and allow them to leave.
6. If they are unsure, allow further time to consider and arrange a convenient date to phone again reiterating that their participation is voluntary. Offer the option to speak to another member of the study team or an independent advisor.
7. All the check boxes within the consent form must be initialled by the patient to confirm they understand each part of the study. Ask the patient to initial each part of the consent form and sign the bottom section adding their name in block capitals.
8. For participants should then be asked post the completed consent form back to the research team in the stamped addressed envelope provided.

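### At sites recruited by the research team, patients who refuse permission to pass on their details never enter the screening log, so there it covers permission-givers only, not all patients

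*Protocol*

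**What the plan says.** Section 4.2.3 of the protocol sets the general rule: "Every patient who plans bariatric surgery will be logged anonymously". The items recorded are age category, gender, planned quarter of surgery, eligibility, consent and planned type of surgery. It then gives the log's aim: "The purpose of this log is to demonstrate if the SCOTS data set is representative of all patients who are having bariatric surgery in Scotland". A second use is to count the patients who consent. The section adds that nothing further is collected on patients who do not wish to take part.

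The sentence stating the general rule carries an exception in brackets for patients identified locally but recruited centrally: "only those giving permission for their details to be forwarded to local teams will have a screening log completed". The reason given is that the log is filled in by the research team in these cases.

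Section 3.6 describes the coverage with no exception: "All patients undergoing bariatric surgery will be recorded on the screening log at their next appointment".

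Two procedural sections fix the order of events at sites with research-team recruitment. At the invitation visit (section 4.2.2.2, step 8): "Patient asked permission for surgical team to pass on contact details to SCOTS research team". In section 4.2.3.2, step 1: "When the Participant Identification Form is received from the surgical team start to complete the SCOTs Recruitment Log and contact the patient via telephone". Step 4 of that section has the screening log completed, and step 5 deals with patients who decline.

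**The concern.** A log meant to show whom the cohort represents needs the people who were not recruited. The first point at which a patient can refuse at a research-team site is the request to pass on contact details. Those refusers are neither counted nor described, so the log cannot show how many there were or whether they differed.

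The log also has two different denominators. At locally recruiting sites it should hold everyone planning surgery; at research-team sites it holds only those who passed the permission step. A consent rate or baseline comparison that did not separate the two would mix them.

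This matters because section 1.3 describes the study as a registry built on objectives rather than hypotheses, so its results are largely descriptive and their use depends on knowing whom they describe. Recruitment stopped at about 400 (section 5.3; 450 in section 2) against the 2000 first proposed, so readers will want to know who was left out.

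**Working it through.** The protocol gives no figure for log coverage, so there is none to reproduce. The check is a reading of the sections together, followed by arithmetic on assumed inputs.

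**Step 1: who is logged at a research-team site.**

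| Patient | Entry on the log? | Basis |
|---|---|---|
| Refuses permission at the invitation visit | No | 4.2.3 exception; 4.2.3.2 starts only when the identification form arrives |
| Gives permission, later declines consent | Yes | 4.2.3.2: log at step 4, declining at step 5 |
| Gives permission and consents | Yes | 4.2.3.2 |

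At locally recruiting sites the general rule in 4.2.3 applies and every patient should be logged.

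**Step 2: which statements conflict.** Section 4.2.3 states the general rule and its exception together, so it discloses the gap. Section 3.6 does not. Its sentence on the log comes after the same paragraph has described recruitment by the research team, so it cannot be read as confined to local recruitment. The conflict is between 3.6 and 4.2.3. There is also tension inside 4.2.3, between the exception and the purpose stated after it. A wording slip should be corrected too: the exception speaks of forwarding details to local teams, whereas 4.2.2.2 sends them to the research team.

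**Step 3: effect within affected sites.** Let r be the share refusing permission (not recorded). With N patients, N(1 - r) are logged. If K consent, the true rate is K/N and the log shows K/[N(1 - r)], so

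apparent rate / true rate = 1/(1 - r).

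- r = 10%: 1/0.90 = 1.11
- r = 20%: 1/0.80 = 1.25
- r = 50%: 1/0.50 = 2.00

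**Step 4: effect across the study, if both routes were combined.** Let s be the share of patients at research-team sites (not stated; section 4 says only that some participants are recruited this way). The unlogged share is s × r. If the combined log shows a consent rate c, the true rate is c × (1 - s × r). With an assumed c = 60%:

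| s | r | Unlogged, s × r | True rate, 60% × (1 - s × r) |
|---|---|---|---|
| 25% | 10% | 2.5% | 58.5% |
| 25% | 50% | 12.5% | 52.5% |
| 50% | 30% | 15% | 51% |
| 75% | 10% | 7.5% | 55.5% |
| 75% | 50% | 37.5% | 37.5% |

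The effect runs from negligible to large, and the protocol does not say where in this range it falls.

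**Step 5: effect on patient mix within affected sites.** If a characteristic is present in a share p of permission-givers and q of refusers, the true share is p(1 - r) + qr, while the log shows p. With assumed p = 30% and q = 50%, the true share is 0.30 × 0.90 + 0.50 × 0.10 = 32% at r = 10%, and 0.30 × 0.50 + 0.50 × 0.50 = 40% at r = 50%. With q = p there is no shift at all. The log holds nothing on q.

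**The case against.** The strongest reply is that the exception is disclosed, with a reason: the research team completes the log at these sites and knows only the patients passed on to it. It affects some sites, later decliners are counted everywhere, and no outcome estimate uses the log, because section 3.3 meets the objectives by comparing patients before and after surgery. Recruitment was due to finish in March 2017 (section 2.2), before this version of November 2017, so the missing entries can no longer be collected prospectively.

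Most of this stands. It limits the point to how participation and representativeness are reported. It does not remove the conflict with section 3.6, and disclosing the exception does not supply the coverage that the log's purpose needs. Privacy is not an evident reason for the gap, since the log is anonymous and refusers at locally recruiting sites are logged in the same way.

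A reader might infer four stronger things that the documents do not support:

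- **The log cannot inform representativeness at all.** It can for locally recruiting sites, and partly for the others.
- **The two routes will be pooled.** Section 5.1 leaves analyses to separate plans that are not shown, so step 4 is conditional on pooling.
- **The cohort will look more similar to the target population than it is.** That depends on whether and how refusers differ, and later decliners could differ in the opposite direction.
- **Coverage can be judged by setting the cohort against the 500 procedures a year in section 5.3.** That was the expectation when the grant was written, and section 1.1 reports that both NHS and private numbers fell. It would also say nothing about the truncation of the log.

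**Conclusion.** The point holds in a limited form. Followed as written, the rule keeps permission-step refusers off the log at research-team sites, contradicts section 3.6 and weakens the log's stated purpose. Participation at those sites is overstated whenever anyone refuses permission, by the factor 1/(1 - r). Neither r nor the share of patients at such sites is given, so no study-wide size can be stated; the figures above only show how it would vary. The direction of any error in the comparison of patient characteristics is unknown. The conclusion assumes that sites kept the log as the protocol describes. It is worth correcting because reporting by route removes the problem at little cost and is still possible after recruitment has closed.

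**What to change.** 1. Reconcile sections 3.6 and 4.2.3 so that both state the same coverage by recruitment route, and correct the wording on which team receives the patient's details.
2. Report log-based consent rates and the representativeness comparison separately by route. Use the log as an all-patient denominator only for locally recruiting sites. For research-team sites, state that it covers permission-givers only and that the number refusing permission is unknown.
3. Optionally, where approvals allow, compare the cohort with aggregate national counts of first bariatric procedures by age band, sex, procedure and quarter. State that these count operated rather than planned patients and may not cover private sites.

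Items 1 and 2 cost a wording change and a split in the reporting tables, provided each log can be assigned to its recruitment route. They need no patient contact. Item 3 is a separate data request: the linkage in section 3.1.1 is for identified study participants and each linkage needs approvals, so aggregate counts of other patients may need approval of their own.
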